#### Other measures

At baseline, participants in the experimental and in the control group will complete: *Demographic*: genre, age, years of education, profession, hospital, work department, years of professional seniority*Ad hoc questionnaire on the use of technological solutions and VR*: individuals will be asked to indicate on a 7-point Likert scale (from “not at all” to “very”): the level of use in general of technological devices, the general level of acceptance of the technology, the level of knowledge of VR, and the level of experience with VR systems.*Ad hoc questionnaire on the level of exposure to COVID-19: *individuals are asked to answer the following questions (“yes”/“no”): Have you ever been caring for COVID-19 patients? Have you ever had family members or friends who became ill with COVID-19? Have you ever had family members or friends who passed away due to COVID-19? Have you ever had any laboratory tests (e.g., serological test, swab) for COVID-19? If you answered “Yes” to the previous question, how many times have you had a laboratory test for COVID-19? Have you ever tested positive for COVID-19? If you answered “Yes,” please indicate how many weeks you have been affected by COVID-19 and the level of severity of symptoms (from 1 “very mild” to 7 “very severe”).*Fear Of Coronavirus (FCOR) *[84]: it consists of a series of statements to measure the level of fear toward the COVID-19 pandemic. The questionnaire is composed of eight items that explore different components of fear, such as the personal experience of concern regarding the current situation, avoidance behaviors, and attention bias. Each statement is evaluated on a 5-point Likert scale.*Ad hoc questionnaire on stress and anxiety management*: 10-item scale developed to assess the use of stress and anxiety management programs and their perceived usefulness (see Table 5).

**Table 5 Tab5:** The ad hoc questionnaire on stress and anxiety management

Questionnaire on stress and anxiety management
**Part 1. Please indicate if (“yes”/ “no”):** • Have you ever followed psychotherapy? • Have you ever followed stress and anxiety management programs? • Since the COVID-19 outbreak, have you ever used remote stress and anxiety management programs (telephone or video)? • Since the COVID-19 outbreak, have you ever used face-to-face stress and anxiety management programs (single or group sessions)?
**Part 2. Rate on a 7-point Likert scale (1 = “not at all,” 7 = “very much”):** • How important in general do you think to have psychological support for stress management and anxiety concerning your profession? • How important do you think it is to have psychological support for managing stress and anxiety in times of emergency, such as those experienced during the COVID-19 crisis? • How important do you feel to follow a stress and anxiety management program at this time in your life? • Have you ever attended meetings about stress and anxiety? • Have you ever searched the Internet for information on stress and anxiety? • Have you ever read books on stress and anxiety?

Besides, with the aim of measuring changes in the affective states of individuals during the intervention, participants of the experimental group will be asked to fill before and after each of the training session the following self-report questionnaires:*State-Trait Anxiety Inventory Form Y-1* (STAI-Y1) [79, 80]: STAY-Y1 addresses state anxiety, which could be defined as a temporary emotional condition characterized by apprehension, tension, and fear about a particular situation or activity. This inventory consists of 20 items on a 4–4-point Likert scale, like the STAI-Y2.*Visual Analogue Scale for Anxiety* (VAS-A) [85, 86] is an instrument that measures state anxiety across a continuum. It is a horizontal line, 100 mm in length, anchored by word descriptors at each end (“no anxiety”; “very severe anxiety”). Individuals mark on the line the point that they feel represents their perception of their current state. The VAS-A score is determined by measuring in mm from the left-hand end of the line to the point that the person marks.

### Data management

Epidemiological and clinical data from each participant will be collected on the CRF by the research psychologist and recorded online all over the study by the study coordinator. Audit trails will be integrated for tracking data entry correction and import procedures for data monitoring. All data gathered during the study will be stored anonymously in a web Central Database Repository. Security and privacy issues will be taken care of according to the individual situation and the participant’s consent. A unique participant number will be assigned to every operator consisting of name and surname first letters and a consecutive number. This unique code will identify all participant-specific data (e.g., epidemiological and clinical study data). Any adverse event will be documented on the CRF. Data access and storage will follow the data security concept of the MS, including password-protected access to all computers and folders. Data will be stored for up to 5 years after the study ends.

### Data analysis

Analysis of variance will be used to evaluate baseline characteristics of the two groups involved in the study, the overall significance of improvement across primary outcome measures, and drop-out versus maintainers. Categorical variables will be compared using Fisher or chi-square tests and continuous variables using *t*-test or Mann–Whitney tests, as appropriate. To assess the effectiveness of the intervention, groups will be compared with a 2 × 2 repeated measure mixed ANOVA for the pre- and post-primary outcome measures (factor Group X factor Time: pre and post). The analysis will be performed for the PSS, STAY-Y2, and DASS-21. A repeated-measures ANOVA (factor Group × factor Time: day of the week) will compare treatment effects within the 1-week intervention for the STAY-Y2 and the VAS-A. Tests of statistical significance and confidence intervals will be two-sided. A *p* < 0.05 will be considered statistically significant. Descriptive methods will be used to report the usability of the intervention for the secondary outcome intervention (i.e., SUS, SDM, NPS, ad hoc questionnaire on difficulties and adverse effects). Data analyses will be carried out through SPSS software.

Recordings from the post-intervention interviews will be transcribed. Two researchers will read the interview transcripts carefully several times to have a sense of the whole data, identifying emerging themes and categories [87]. A codebook will be created and modified until the final set of codes is obtained and reached to the data saturation point when there is no emergence of other new themes. Qualitative data analysis will be conducted using a thematic content analysis approach following a systematic process. Codes will be applied to the transcripts and converted into categories to represent the main themes arising from the data [88]. Triangulation of themes and concepts will be used to compare further and contrast the data from the different participating groups. Codes will be applied to the transcripts and converted into categories to represent the main themes arising from the data [88].

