### Sample size

Power size calculation was performed with GPower 3.1. Considering an anticipated effect size (*f*) of.25, an alpha set at 0.05, 2 groups, and a 0.95 statistical power, the total sample size required is *N* = 54. We, therefore, plan to enroll a total of 60 participants, which should guarantee a proper sample even in case of drop-outs.

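### As written, the pre/post ANOVA uses only participants with both scores, and the one named drop-out comparison is too weak to show whether that matters

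*Protocol article*

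**What the plan says.** All references are to the protocol article.

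- **Effectiveness model (Data analysis).** Groups are compared with a "2 × 2 repeated measure mixed ANOVA for the pre- and post-primary outcome measures", with factors Group and Time (pre and post), for the PSS, the trait anxiety scale and the DASS-21.
- **Drop-out analysis (Data analysis).** Analysis of variance is also to evaluate "the overall significance of improvement across primary outcome measures, and drop-out versus maintainers". The text does not say which variables are compared or whether arm is a factor. The threshold is p < 0.05, two-sided.
- **Numbers (Sample size).** With f = 0.25, "an alpha set at 0.05, 2 groups, and a 0.95 statistical power", the requirement is 54. Sixty are enrolled, "which should guarantee a proper sample even in case of drop-outs". No drop-out rate is given.
- **Schedule (Table 2).** PSS-10, STAI-Y2 and DASS-21 are collected at baseline, week 1 and week 5, and the Outcomes section has both arms complete them.
- **Other provisions.** Reminders and phone calls are planned, the date and reason of each withdrawal are recorded, and drop-outs count as adherence data (sections on adherence strategies, withdrawal and secondary outcomes).

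**The concern.** A classical pre/post ANOVA without imputation needs both scores from each person. A participant who misses week 1 but returns the week-5 scales therefore contributes nothing, and the baseline score is discarded too. Extra enrolment restores the number analysed but does not make those who remain representative of those randomised.

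Reasons for leaving can plausibly differ by arm. Only the VR arm has home sessions, a return visit and possible VR side effects. Controls know that they receive no training, and the primary outcomes are self-completed. If leaving depends on baseline stress in one direction in one arm and in the other direction in the other arm, the completers' mean changes are no longer comparable, because high scorers tend to fall and low scorers to rise whatever the treatment.

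The named comparison of leavers with stayers is the natural place to look for this. With few leavers it has little power, so a non-significant result would say little about whether the effect estimate is distorted.

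**Working it through.** **1. The plan's sample size.** The inputs f = 0.25, alpha 0.05, 2 groups and power 0.95 come from the Sample size section. Two measurements (m) and a pre-post correlation of 0.5 (r) are not stated and are assumed here. For the Group × Time interaction, λ = f²·N·m/(1 − r) = 0.0625 × 54 × 2 / 0.5 = 13.5 on 1 and 52 degrees of freedom, which gives power 0.9501. So N = 54 reproduces exactly for the 2 × 2 model. The implied allowance is 60 − 54 = 6.

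**2. Power of the leaver/stayer comparison.** For two groups, ANOVA is a t-test. With 6 against 54, the noncentrality is d/√(1/6 + 1/54) = d/0.430 and the critical t on 58 degrees of freedom is 2.002.

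| Difference d (SD) | Noncentrality | Power |
|---|---|---|
| 0.2 | 0.46 | 7% |
| 0.5 | 1.16 | 21% |
| 0.8 | 1.86 | 45% |
| 1.0 | 2.32 | 63% |
| about 1.23 | 2.86 | 80% |

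**3. If the arms are pooled.** Assume three leavers per arm, D above the arm mean in one arm and D below it in the other. The pooled leaver mean then equals the overall mean. In simulation (8,000 trials) the pooled test rejects in 4.9%, 3.7% and 3.9% of trials for D = 0.5, 0.8 and 1.0, no more than alpha. The baseline gap between the completers of the two arms is 2 × D × 3/27 = 0.11, 0.18 and 0.22 SD. A drop-out-by-arm interaction would reject in 25%, 53% and 72%, so it is better but still weak at moderate D.

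**4. Effect on the stated ANOVA.** Assume no true effect, normal scores with SD 1 and no later data from leavers. The three highest-baseline VR participants and the three lowest-baseline controls leave.
- Removing the top 3 of 30 moves the mean baseline of those who stay by about 0.187 SD. Controls move by the same amount the other way.
- Expected change is −(1 − r) × baseline, so the bias in the group difference is 2 × (1 − r) × 0.187. At r = 0.5 this is 0.187 (simulations gave 0.18 to 0.19). At r = 0.3 it is 0.26 and at r = 0.7 it is 0.11.
- At r = 0.5 the change score has SD 1. The standard error with 27 per arm is √(2/27) = 0.272, and 0.187/0.272 = 0.69. The normal approximation gives a rejection rate of Φ(−1.27) + Φ(−2.65) ≈ 0.11, and simulation also gives 11%.
- A pooled baseline check flags practically none of these trials.
- A likelihood estimate that keeps all 60 baselines has essentially zero bias.

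In this pattern the bias runs against VR. With the tails swapped it favours VR by the same amount.

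**5. A harder case.** If leaving depends on the change itself, which is unseen for leavers, losing the worst-changing 3 of 30 VR participants moves the VR mean by 0.19 SD. False positives become about 12% with random control loss, and about 36% if controls also lose their three best. At r = 0.5 the likelihood model keeps about 77 to 80% of this bias.

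**The case against.** **Scope.** The document is a condensed article, and rules for missing data, analysis sets and sensitivity analyses commonly sit in the full protocol or SAP. This stands: their absence is not a finding, and the article gives no rule for missing post scores. The point rests on the model that the article does name, whose unimputed form needs both scores.

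**Arm structure.** The text does not say that the arms are pooled, and an ANOVA with arm and drop-out status would fit its wording. The planned Fisher or chi-square tests could also compare drop-out counts. Pooling is therefore a reading, although the authors write out Group as a factor elsewhere in the same paragraph and not here. Count tests help only in extreme splits: Fisher gives p = 0.024 for 6 against 0, but 0.19 for 5 against 1 and 0.67 for 4 against 2. They also say nothing about who leaves.

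**Other protection.** A reader might infer that this comparison is the trial's only safeguard. It is not, given the over-enrolment, reminders, calls, recorded reasons and adherence reporting. It is the only drop-out analysis named.

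**Six losses.** Six is the cushion, not a forecast.

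**Strength of the check.** A reader might also infer that it can never flag a problem or never see arm-specific loss. The figures do not support that: power is 45% at 0.8 SD and 63% at 1.0 SD, and a large difference confined to one arm can show. Nor does the article say that a null result will be taken as proof of no bias.

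**Conclusion.** The concern holds in a limited form. The stated effectiveness model discards usable scheduled data and is biased when drop-out depends on baseline differently in the two arms. In the assumed pattern of three leavers per arm the bias is about 0.18 to 0.19 SD with about 11% false positives (0.11 to 0.26 SD for pre-post correlations of 0.7 to 0.3). The pattern is illustrative and the documents do not predict it.

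The leaver/stayer ANOVA gives little reassurance at six losses, and if pooled it is uninformative about opposite differences in the two arms. A non-significant result should not be read as evidence against attrition bias.

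The 12% and 36% rates are worst-case illustrations of loss driven by unseen scores. They do not measure the cost of omitting arm from the check, and the mixed model does not cure them. This is a worthwhile, inexpensive improvement to a stated method, not an error that invalidates the design.

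**What to change.** In the Data analysis section:

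1. Fit the effectiveness analysis as a likelihood-based mixed model on all randomised participants, using the baseline, week-1 and week-5 scores, with Group × Time and the week-1 contrast as the main comparison. With complete data and an unstructured covariance, the estimated contrast equals the 2 × 2 interaction, so the basis of the sample size is unchanged.
2. Replace reliance on the drop-out significance test with a descriptive table by arm: number of leavers, reasons, and baseline PSS-10, STAI-Y2 and DASS-21 for leavers and stayers. State that a non-significant comparison is not evidence against attrition bias.
3. Optionally, add a sensitivity analysis that worsens the VR leavers' imputed scores stepwise until the conclusion changes.

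The cost is wording and slightly more analysis work. SPSS fits such models, and the scores and withdrawal reasons are already collected. The limit is that the model does not remove bias from drop-out that depends on unseen post scores; only an analysis such as item 3 explores that.

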### Design and setting

The study will follow a 2-arm, parallel-group, RCT model. A total of 60 consecutively enrolled individuals (see the “Sample size” section for the power calculation) will be recruited from healthcare workers of three Medical Sites (MS) in Italy: the Foundation IRCCS Carlo Besta Neurological Institute Foundation (Milan, Italy), the Fondazione Europea Ricerca Biomedica (FERB) (Gazzaniga, Italy), and the Istituto Santa Lucia (Roma, Italy). In each MS, 20 participants will be recruited among hospital units that treat or have treated COVID-19 patients (i.e., the emergency department, surgical units, and critical care units).

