### Randomization

The study coordinator will prepare the randomized sequence with a block randomization procedure using a true random number generator: www.randomizer.org. The randomized list will be created using a reasonably sized permuted block method, the block size of which will not be disclosed until the end of this trial to ensure concealment.

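### The planned Group × Time ANOVA is valid but uses baseline inefficiently: adjusting the post score for baseline would cut the error variance by about 25% if the pre-post correlation is 0.5

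*Protocol article*

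**What the plan says.** The Data analysis section names the effectiveness test: "To assess the effectiveness of the intervention, groups will be compared with a 2 × 2 repeated measure mixed ANOVA". Its two factors are the arm and the visit, with one measurement before and one after the training. The section then lists the scales: "The analysis will be performed for the PSS, STAY-Y2, and DASS-21". No baseline-adjusted model is named for them.

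The Allocation section has participants fill in the baseline questionnaires at the screening interview, before the step in which they are randomised. Baseline scores are therefore pre-randomisation measurements and legitimate covariates.

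The Sample size section gives its inputs as "Considering an anticipated effect size (*f*) of.25, an alpha set at 0.05, 2 groups, and a 0.95 statistical power". It arrives at N = 54 and raises enrolment to 60 to allow for drop-outs. It states no pre-post correlation.

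**The concern.** The article fixes the analysis model in so many words, so this is not a detail left to a statistical analysis plan. With one pre and one post measurement, the Group × Time interaction is the two-sample t-test on the change score. That test subtracts the whole baseline value, which is the best use of baseline only if the regression slope of post on pre is 1. With r below 1 and similar spread at both visits the slope is below 1, and subtraction adds noise that a fitted slope would avoid.

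What is at stake is precision. The trial collects baseline on everyone, has only 60 participants, and would get wider intervals than the same data allow.

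**Working it through.** **Inputs.** From Sample size: f = 0.25, alpha 0.05, power 0.95, two groups, N = 54, enrolment 60. From Data analysis: two time points and two-sided tests. From Allocation: 1:1. Assumed, because it is not stated: the pre-post correlation r, taken as 0.5 with a range of 0.3 to 0.9, and equal SDs (σ) before and after.

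**1. Reproduce N = 54.** For the interaction with m = 2 measurements, the noncentrality is λ = f²·N·m/(1−r), with 1 and N−2 degrees of freedom. At r = 0.5 and N = 54, λ = 0.0625 × 54 × 2/0.5 = 13.5, and power is 0.9501. The stated figure is reproduced. Other correlations give other sizes for the same test: 66 at r = 0.4 and 44 at r = 0.6. So r = 0.5 is the value that fits the planned 2 × 2 interaction.

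**2. What effect that is.** For the change-score t-test, λ = δ²·N/(4·2(1−r)), with δ in SD units. Equating this with 2f²N/(1−r) gives δ = 4f = 1.0 SD. The planned effect is a between-group difference in change of one SD.

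**3. Compare the error variances.**
- Change score: 2(1−r)σ²
- Post score adjusted for baseline: (1−r²)σ²
- Ratio: (1−r²)/[2(1−r)] = (1+r)/2

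The difference, 2(1−r) − (1−r²) = (1−r)², is positive for every r below 1.

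| r | Variance ratio | Cut in variance |
|---|---|---|
| 0.3 | 0.65 | 35% |
| 0.5 | 0.75 | 25% |
| 0.7 | 0.85 | 15% |
| 0.8 | 0.90 | 10% |
| 0.9 | 0.95 | 5% |

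At r = 0.5 the standard error falls by 1 − √0.75 = 13.4%. Unadjusted, the same precision would need 1/0.75 = 1.33 times as many participants.

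**4. Finite-sample check.** A simulation of 4,000 trials per correlation at N = 54 gave mean estimated variances of 0.0737 (change) and 0.0565 (ANCOVA) at r = 0.5, a ratio of 0.767, or a 23% cut. The cut was 13% at r = 0.7 and 8% at r = 0.8. With no true site effect, adding site left the ratio at 0.767.

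**5. Power at N = 60.**
- Planned effect (1.0 SD), r = 0.5: λ is 15 for the change score (58 df) and 15/0.75 = 20 for ANCOVA (57 df). Power goes from 96.8% to 99.3%. With site as well (55 df) it is 0.9925 instead of 0.9926.
- Illustration at 0.5 SD, r = 0.5: the t noncentrality is 0.5 × √15 = 1.94 against 1.94/√0.75 = 2.24. Power goes from 47.8% to 59.4%.
- Illustration at 0.5 SD, r = 0.8: power goes from 85.3% to 88.7%.

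For 95% power at the planned effect and r = 0.5, N falls from 54 to 42.

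**The case against.** The strongest reply is that nothing here is an error. The change-score test is unbiased under randomisation, and the sample size calculation fits exactly that test. At the planned effect the trial already has 96.8% power at full enrolment, so the gain there is small. The 0.5 SD figures rest on an effect that the article does not mention. All of this stands: the point is about efficiency.

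The size of the gain is also open. A trait scale such as the STAI-Y2, retested after about a week, may well have a high r, and then the gain is only 5% to 10%. It may differ across the three scales. This stands too, so 25% must be read as conditional on r = 0.5.

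A reader might infer three stronger things that the document does not support.

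- *Hospital differences are confounded with arm.* The Design and setting section does fix the site sizes ("In each MS, 20 participants will be recruited among hospital units that treat or have treated COVID-19 patients"), but change scores already cancel stable differences in level between hospitals. Only site differences in one-week change could matter, and no figure for these is given. The Randomization section says "The randomized list will be created using a reasonably sized permuted block method" and does not say whether there is one list or one per site, so an unstratified list cannot be assumed.
- *The group main effect, which averages in the pre-randomisation score, will be read as the treatment effect.* The article specifies Group by Time and nowhere says this.
- *Site adjustment contributes to the 25%.* All of it comes from baseline.

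**Conclusion.** The planned test is valid but gives up precision that baseline adjustment would recover. The variance ratio is (1+r)/2, assuming equal SDs at the two visits. The cut is about 25% at r = 0.5, a correlation inferred from N = 54 and not stated in the article, and it shrinks towards zero as r approaches 1. The practical benefit is modest if the true effect is near 1.0 SD and larger if it is smaller. This is a worthwhile improvement at almost no cost. It gives no reason to distrust a result from the ANOVA as planned.

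**What to change.** Replace the 2 × 2 ANOVA sentence with wording such as: *For PSS, STAI-Y2 and DASS-21, the post-intervention score will be compared between groups by ANCOVA with the baseline score of the same scale as covariate; the adjusted mean difference with its 95% CI is the treatment effect.*

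The cost is one sentence and one residual degree of freedom, and the named software can fit the model. Site may be added as a fixed factor for two more degrees of freedom, on design grounds and without a promised gain. The allocation procedure stays as it is. Recruitment was under way at submission and no interim analysis is planned, so the change should be recorded through the article's amendment route before outcomes are examined by arm. Stating the assumed pre-post correlation in the Sample size section would let readers check both N = 54 and the expected gain.

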### Withdrawn criteria

Participants will be considered withdrawn if any of the following occurs: (1) participant chooses to withdraw from the study at any time, (2) intolerable adverse effects, (3) major violation of the study protocol, and (4) other circumstances that would endanger the health of the subject if he/she were to continue his/her participation in the trial. The date and reason for withdrawal will be documented in a paper-and-pencil case report form (CRF).

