#### Experimental group

Participants in the experimental group will receive the home-based VR intervention. Following a description of the protocol in detail:*Intake session (session 1):* after signing the informed consent and completing the baseline questionnaire accessible online (i.e., demographic, ad hoc questionnaire about the use of technological solutions and VR, ad hoc questionnaire on the level of exposure to COVID-19, FCOR, ad hoc questionnaire on stress and anxiety management, PSS-10, STAI-Y2, DASS-21, ad hoc questionnaire on knowledge of stress and anxiety), participants will receive from the research psychologist an explanation about the aims and methods of the home-based VR program. Participants will be asked for their involvement and availability during a week to allow in-home training. The psychologist will remind participants to perform the training three per week, with a distance of 2 days between one session and another. Then, individuals will receive information about the safety and hygiene procedures to prevent COVID-19 infection (see Table 3). The psychologist will give participants the Oculus Quest 2, a consumer-grade standalone VR system that consists of an HMD and two controllers. Individuals will wear the headset and receive a short 15-min training on using the VR system. In particular, they will try the tutorial content available on the Oculus Store. Furthermore, individuals will receive a link to complete the online questionnaires (i.e., STAI-Y1, VAS-A) before and after each session. They will be provided with a log book in which to record technical problems, safety issues, and the date and time they used VR during the intervention. Finally, the research psychologist will schedule the date of the post-training session.*Training sessions (sessions 2, 3, and 4):* they will consist of three home sessions of approximately 30 min each, conducted in a week with a distance of 2 days between one session and another. Participants will try for about 15 min one path of the virtual psychoeducational experience MIND-VR in each session (see Fig. 2). Subsequently, they will use for about 10 min the virtual relaxation content The Secret Garden. Individuals will be asked to complete online the VAS-A and the STAI-Y1 at the beginning and the end of each session.*Post-training session (session 5):* the research psychologist will meet participants for the post-intervention interview at the end of the training. On this occasion, participants will return the Oculus Quest 2, which will undergo specific procedures to avoid contamination by COVID-19. Participants will be asked to complete within 1 week after completion of the intervention the online questionnaires (i.e., PSS-10, STAI-Y2, DASS-21, ad hoc questionnaire on knowledge of stress and anxiety, SUS, SDM, NPS, ad hoc questionnaire on difficulties and adverse effects).*Follow-up session (session 6):* the PSS-10, STAI-Y2, DASS-21, and the ad hoc questionnaire on knowledge of stress and anxiety will be conducted after a 1-month follow-up.

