#### Control group

This group will undergo baseline, post-intervention, and follow-up assessments without undergoing any training during the 1-week intervention period.

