### Outcomes

#### Primary outcome measure

At baseline, post-intervention, and follow-up, participants in the experimental and in the control group will complete the following questionnaires that will serve as the primary outcome measures:*Perceived Stress Scale* (PSS-10) [77, 78]: the PSS is a 10-item self-reported measure to assess the current stress level using a 5-point Likert scale.*State-Trait Anxiety Inventory Form Y-2 (STAI-Y2)* [79, 80]: a validated and widely used measure of trait anxiety. Individuals are asked to specify to which extent, on a 4-point Likert scale (from “not at all” to “very much”), they usually perceive each of the 20 indicated feelings.*The Depression, Anxiety and Stress Scale-21 Items (DASS-21)* [81]: is a set of three self-report scales designed to measure depression, anxiety, and stress symptoms. Each of the three scales contains seven items, divided into subscales with similar content. The scores for depression, anxiety, and stress are calculated by adding up the scores for the relevant items.Ad hoc* questionnaire on the knowledge of stress and anxiety*: individuals are asked to rate on a 7-point Likert scale (1 = “not at all,” 7 = “very much”) knowledge about the differences between anxiety and stress, causes and symptoms of stress and anxiety, and techniques for the management of these conditions. Besides, participants complete 5 factual questions in multiple-choice format (e.g., “Which is the first phase of the General Adaptation Syndrome?”) and 2 conceptual questions in short-answer format (e.g., “What are the three main categories of stress symptoms?”). The questions are based on the methodology used in a previous study (Parong and Mayer, 2018) (see Table 4).

**Table 4 Tab4:** The ad hoc questionnaire on the knowledge of stress and anxiety

Questionnaire on the knowledge of stress and anxiety
***Part 1. Rate on a 7-point Likert scale (1***** = *****“not at all,” 7***** = *****“very much”) your level of knowledge about*****:** • The differences between anxiety and stress • Causes and symptoms of stress and anxiety • Techniques for the management of stress and anxiety

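### Stress and anxiety scores are primary outcome measures at week 5 in both arms, but the effectiveness analysis stops at week 1 and no analysis is specified for week 5

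*Protocol article*

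**What the plan says.** The Primary outcome measure section states: "At baseline, post-intervention, and follow-up, participants in the experimental and in the control group will complete the following questionnaires", and describes these as the instruments "that will serve as the primary outcome measures". They are the PSS-10, STAI-Y2, DASS-21 and an ad hoc knowledge questionnaire. Table 2 marks all four at weeks 0, 1 and 5.

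The arm descriptions agree. For the experimental group, "the PSS-10, STAI-Y2, DASS-21, and the ad hoc questionnaire on knowledge of stress and anxiety will be conducted after a 1-month follow-up". For the control group, "This group will undergo baseline, post-intervention, and follow-up assessments without undergoing any training". The section on adherence strategies adds email and text reminders for the follow-up assessment, and phone calls to those who do not respond.

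The Data analysis section assesses effectiveness with "a 2 × 2 repeated measure mixed ANOVA for the pre- and post-primary outcome measures (factor Group X factor Time: pre and post", and lists the PSS, the STAI trait form (printed there as STAY-Y2) and the DASS-21 as the outcomes to be analysed this way. A second repeated-measures ANOVA is confined to the one-week intervention. One further sentence gives analysis of variance for the overall significance of improvement in the primary outcome measures, without naming a time point.

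**The concern.** Design and analysis disagree about how many occasions the primary outcomes have. This is more than detail left to a statistical analysis plan, because the article itself fixes the Time factor and fixes it at two levels, after declaring three occasions for the same instruments.

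Week 5 is the only randomised evidence on whether an effect outlasts the training week. The Discussion section looks that far ahead: it suggests that a significant reduction could make the training a viable option both during the pandemic and after it. If the plan is followed as written, a week-5 comparison would be chosen after the data are seen. With no primary time point named, the choice between a week-1 and a week-5 headline also stays open.

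**Working it through.** **Occasions collected against occasions analysed (both arms)**

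| Occasion | PSS-10, STAI-Y2, DASS-21 collected | In the stated effectiveness ANOVA |
|---|---|---|
| Baseline, week 0 | yes | yes (pre) |
| Post-intervention, week 1 | yes | yes (post) |
| Follow-up, week 5 | yes | no |

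The other repeated-measures ANOVA ends with the intervention week, so it cannot reach week 5.

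**Size of the gap.** 60 participants × 3 instruments = 180 follow-up questionnaires at most. The knowledge questionnaire is not counted. The list of outcomes for the ANOVA omits it at every time point, which is a separate matter.

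**The plan's sample size.** The Sample size section gives f = 0.25, alpha 0.05, 2 groups, power 0.95 and N = 54. It does not state the number of measurements m or the correlation ρ between them. For the group-by-time interaction, the noncentrality is λ = f² × N × m / (1 − ρ), with (k − 1)(m − 1) and (N − k)(m − 1) degrees of freedom and k = 2. Sphericity is assumed.

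- m = 2, ρ = 0.5 (assumed): λ = 0.0625 × 54 × 2 / 0.5 = 13.5 on 1 and 52 df. Power is 0.950, so N = 54 is reproduced.
- m = 3, ρ = 0.5: N = 44 is enough. λ = 0.0625 × 44 × 3 / 0.5 = 16.5 on 2 and 84 df; power is 0.956.

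At ρ = 0.5 the stated N matches a two-occasion design, like the ANOVA and unlike the data collection.

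**Can the planned sample support a week-5 comparison?** Power of a baseline-to-follow-up 2 × 2 contrast at f = 0.25:

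| Assumed ρ | N = 54 | N = 60 |
|---|---|---|
| 0.3 | 0.862 | 0.896 |
| 0.5 | 0.950 | 0.968 |
| 0.7 | 0.996 | 0.998 |

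No increase in sample size is needed at ρ = 0.5.

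**Participants used under each repair.** The protocol gives no dropout rate. Suppose, for illustration, that 10% are missing independently at each of weeks 1 and 5, with baseline complete because it precedes randomisation.

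- Repeated-measures ANOVA with three Time levels, complete cases only: 0.9 × 0.9 = 0.81, and 0.81 × 60 = 48.6, about 49 participants.
- Mixed model, at least one post-baseline visit: 1 − 0.1² = 0.99, and 0.99 × 60 = 59.4, about 59 participants.

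**The case against.** The strongest reply has three parts, and each partly stands.

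- **The sentence on overall improvement might cover follow-up.** It names no time point, and the measures it refers to are defined at all three. An unseen analysis plan might also cover week 5. So the accurate statement is that no week-5 analysis is specified in this document. A reader might infer that persistence will never be tested or can never be assessed; the text does not support that, because the data are collected in both arms. The gap is in prespecification.
- **Durability is not a stated aim.** The Objectives section lists no separate durability objective. The point rests instead on week 5 being a declared occasion for primary outcome measures.
- **A mixed model is a preference.** Correct. A reader might think that extending the ANOVA to three Time levels would not repair the gap. It would, since either that or a baseline-to-follow-up contrast tests week 5. Nor does keeping about 49 complete cases fall short of a required 54, because 54 is the two-occasion figure. With three occasions 44 suffice at ρ = 0.5, and power at N = 49 is 0.973. The mixed model is better because it uses more of the randomised participants.

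A reader might also link this to the Withdrawn criteria, where one ground is "3) major violation of the study protocol", and infer that poorly adhering VR participants would be dropped and the comparison biased toward VR. The documents do not say so. That section says when a participant counts as withdrawn and that the date and reason are recorded; it does not remove data from any analysis. Missed sessions are met with reminders and calls, and adherence is itself assessed. No violation rate is given from which a bias could be calculated.

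**Conclusion.** The point holds in a limited form. Three instruments are primary outcome measures at three occasions in both arms, and the only specified effectiveness analysis uses two of them. Up to 180 follow-up questionnaires have no prespecified between-group comparison, and no primary time point is named. The week-1 comparison is unaffected and the stated N = 54 is not wrong.

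The mismatch rests on the text alone. The power figures depend on an assumed ρ and on f = 0.25 applying at week 5 as well. The 99% against 81% comparison depends on the assumed 10% independent missingness; it supports the choice of repair and is not needed to establish the gap. This should be corrected before analysis, but it does not invalidate the trial.

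**What to change.** Amend the Data analysis section to:

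1. Name week 1 as the primary time point and week 5 as key secondary.
2. Prespecify the between-group comparison at week 5 for the PSS-10, STAI-Y2 and DASS-21.
3. Preferably replace the 2 × 2 ANOVA with one linear mixed model per outcome for weeks 1 and 5: baseline value as covariate; group, time and group × time; all randomised participants in their assigned arm. Report the adjusted group difference with its confidence interval at each week.
4. As a minimum, keep the ANOVA and add follow-up as a third Time level, or add a baseline-to-follow-up contrast.

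The cost is wording and a standard procedure in SPSS, the software already named. No visits, questionnaires or participants are added. The small downside is one more prespecified test per outcome, which the primary and key secondary labels should make explicit. The Trial status section reports recruitment still ongoing at submission, so the amendment should be dated and registered before outcome data are analysed. If that point has passed, week-5 comparisons should be labelled post hoc.
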